#### 3.5.2 Withdrawal from Trial

In many circumstances where a patient withdraws from trial treatment, it will, nonetheless, be desirable for the patient to remain on the trial (for example for follow-up purposes). If, however, the patient withdraws from the trial itself, it should be clearly documented in the patient's notes what they are withdrawing from (consent to use any past data, consent to use any samples collected or consent for further data collection from the date of consent withdrawal). If a patient withdraws their consent from the trial, the site must contact the CRUK CTU Glasgow with full details of the withdrawal. Where applicable, the CRUK CTU Glasgow may ask the site to complete a Consent

Withdrawal Form to record full details of the consent withdrawal. In the event of withdrawal, data or tissue already collected with consent will be retained and used in the study, but no further tissue will be collected or any other research procedures carried out on or in relation to the participant.

Patients who become unwell to such an extent that they lose capacity during the course of the study will be permitted to continue on IMP until the point they are unable to swallow oral medication, and all other study processes, including safety assessments, should continue. No patient whether they have capacity or not will continue on the trial if it is unsafe to do so in the opinion of the Principal or Chief Investigator, or the Trial Steering Committee.

## **4 TRIAL PROCEDURES**

### **4.1 Trial Endpoints**

The trial endpoints are defined in Section 2.

### **4.2 Trial Schedule**

Below is a list of expected assessments for each patient entered into the GETAFIX trial and the relevant time points. Assessments marked with asterisk (\*) are considered part of standard care.

#### **4.2.1 Schedule for Inpatients**

##### **Initiation of screening to first dose**

Written informed consent

Assessment of eligibility criteria

Demographic details

Valid COVID-19 diagnostic test

Medical history including assessment of medical co-morbidities

Documentation of concomitant medications

Clinical examination (performed by Principal Investigator or their designee)

Human chorionic gonadotrophin (serum HCG) test to rule out pregnancy at trial entry; results must be obtained and reviewed before randomisation for women of childbearing potential.

Routine observations\* (see Table of assessments for detail)

Routine clinical blood tests\* (see Table 2)

Height and weight\*

Pre-morbid performance status as assessed by WHO criteria (Appendix 2)

WHO COVID 10 point ordinal severity scale assessment (Appendix 1)

### **Day 1-10^1**

WHO COVID 10 point ordinal severity scale assessment (daily – worst value in last 24 hours)

Documentation of concomitant medications (daily)

Assessment of adverse events (daily)

Routine observations/vital signs\* (daily)

Routine clinical blood tests: days 1,3,8,11 (+/- 48 hours)

Blood tests for immunological and epigenetic testing: days 1, 3 (+/- 48 hours)

Symptom directed clinical examination if clinically indicated

Administration of IMP (if applicable)

Nasopharyngeal swab (for SARS-CoV-2 PCR assessment and Viral Load): days 1 (at time of first dose), 3, 8, 10, 13 (+/- 48 hours)

Pharmacokinetic samples: according to the sample schedule (Appendix 5)

 Patients discharged during this time should follow the outpatient trial schedule. The timing of the first dose of favipiravir should be documented as Time zero (T0). The nasopharyngeal swab should be taken as close to this time as possible.

 On day 8, two swabs should be taken – one to be sent for immediate COVID-19 testing by any valid method, the other to be stored for later analysis of viral load.

### **Day 15**

Nasopharyngeal swab (for SARS-CoV-2 PCR assessment and Viral Load) (+/- 48 hours)

WHO COVID 10 point ordinal severity scale assessment (Appendix 1).

Routine clinical blood tests

Blood tests for immunological and epigenetic testing (+/- 48 hours)

Pharmacokinetic samples- according to the sample schedule (Appendix 5)

## COVID-19 Health and Wellbeing Follow up Survey (Appendix 3)

Day 15 assessment should be done in clinic if patient has been discharged. If patient is unable to attend clinic, a follow-up telephone assessment should be done.

Optional if patient unable to attend clinic

### **Day 29 and Day 60^1**

Assessment of concomitant medication and adverse events to be undertaken by an investigator with the patient.

Routine clinical blood tests

Blood tests for immunological and epigenetic testing

WHO COVID 10 point ordinal severity scale assessment (Appendix 1)

Nasopharyngeal swab (for SARS-CoV-2 PCR assessment and Viral Load)

Concomitant medications

Assessment of adverse events

COVID-19 Health and Wellbeing Follow up Survey (Appendix 3)

Day 29 and Day 60 assessments should be done in clinic if patient has been discharged. If patient is unable to attend clinic, a follow-up telephone assessment should be done.

Optional if patient unable to attend clinic

## **4.2.2 Schedule for outpatients**

### **Initiation of screening to first dose**

Written informed consent

Assessment of eligibility criteria

Demographic details

Valid COVID-19 diagnostic test

Medical history including assessment of medical co-morbidities

Documentation of concomitant medications

Clinical examination (performed by Principal Investigator or their designee)  
Human chorionic gonadotrophin (serum HCG) test to rule out pregnancy at trial entry; results must be obtained and reviewed before randomisation for women of childbearing potential.  
Routine observations (see Table of assessments for detail)  
Routine clinical blood tests (see Table 2)  
Height and weight  
Pre-morbid performance status as assessed by WHO criteria (Appendix 2)  
WHO COVID 10 point ordinal severity scale assessment (Appendix 1)  
Baseline PK sample

### **Day 1-10^1**

Dispensing of IMP (patients on favipiravir arm)  
WHO COVID 10 point ordinal severity scale assessment (daily – worst value in last 24 hours)  
Documentation of concomitant medications (daily)  
Assessment of adverse events (daily)  
Nasopharyngeal swab (for SARS-CoV-2 PCR assessment and viral load): day 8  
Administration of IMP and completion of Patient Diary (patients on favipiravir arm)

 Assessments on day 1-10 will be performed by telephone

 IMP may be dispensed in clinic following randomisation where possible, or couriered to the patient's home

 NP swab may be performed at home by the patient provided this is safe to do and safe transport to research laboratory has been arranged.

 Baseline PK sample can be taken at screening or pre-dose day 1. PK sampling will only be undertaken where sites can accommodate both pre and post dose sampling, and have the facilities to spin samples within 4 hours.

### **Day 15**

Nasopharyngeal swab (for SARS-CoV-2 PCR assessment and Viral Load) (+/- 48 hours)  
WHO COVID 10 point ordinal severity scale assessment (Appendix 1).  
Routine clinical blood tests  
Blood tests for immunological and epigenetic testing (+/- 48 hours)  
End of Treatment Compliance check - return of any remaining IMP/empty container, and completed diary (favipiravir arm only)

## COVID-19 Health and Wellbeing Follow up Survey (Appendix 3)

 Day 15 assessment should be done in clinic - if patient is unable to attend clinic, a follow-up telephone assessment should be done.

 Optional if patient unable to attend clinic

 Compliance check should be done at next follow-up visit if patient cannot attend on day 15

### Day 29 and Day 60^1

Assessment of concomitant medication and adverse events to be undertaken by an investigator with the patient.

Routine clinical blood tests

Blood tests for immunological and epigenetic testing

WHO COVID 10 point ordinal severity scale assessment (Appendix 1)

Nasopharyngeal swab (for SARS-CoV-2 PCR assessment and Viral Load)

Concomitant medications

Assessment of adverse events

COVID-19 Health and Wellbeing Follow up Survey (Appendix 3)

 Day 29 and Day 60 assessments should be done in clinic if patient has been discharged. If patient is unable to attend clinic, a follow-up telephone assessment should be done.

 Optional if patient unable to attend clinic

**Table 2:** Routine clinical blood tests

| Haematology          | Biochemistry         |
|----------------------|----------------------|
| Haemoglobin          | Urea                 |
| WCC and differential | Creatinine           |
| Haematocrit          | Potassium            |
| Platelets            | Sodium               |
|                      | AST                  |
| APTT                 | ALT                  |
| PT                   | Alkaline phosphatase |
| PT ratio             | Bilirubin            |
| APTT ratio           | Albumin              |
| Thrombin time        | Uric acid            |
| TCT ratio            | Magnesium            |

|                                   |                                                                                                                                              |
|-----------------------------------|----------------------------------------------------------------------------------------------------------------------------------------------|
| Fibrinogen
D-Dimer
Ferritin | Calcium
Phosphate
Chloride
Bicarbonate
CRP
NT proBNP
High Sensitivity Troponin
HbA1c
Lipids
HDL-c
Anti-DNA/ANA |
|-----------------------------------|----------------------------------------------------------------------------------------------------------------------------------------------|

### 4.3 Laboratory Tests

#### 4.3.1 Routine blood tests

Routine blood tests will be collected at site and sent to local NHS laboratories for processing. All laboratory tests will be conducted according to local procedures.

#### 4.3.2 Valid COVID19 Test for diagnosis and viral clearance

An appropriate sample (usually a nasopharyngeal swab) will be collected and sent to local NHS laboratories for processing for diagnosis. Viral clearance on day 8 for inpatients will also be processed at a local NHS laboratory. Viral clearance at day 8 for outpatients will be collected at home by patients and sent to local academic laboratories for processing, provided it is feasible and safe to do so.

#### 4.3.3 Viral Load for pharmacodynamics

A nasopharyngeal swab will be collected and sent to local Academic laboratories for processing. Viral PCR testing will be conducted according to local procedures.

#### 4.3.4 Pharmacokinetic/Pharmacodynamic sampling

Immunological, transcriptomic and epigenetic markers and plasma concentration of favipiravir for pharmacokinetic analysis : 1 tubes of EDTA blood and a Paxgene tube will be sent to local academic and NHS laboratories for safe processing and aliquots processed to generate plasma, PBMC and a whole blood layer which will be stored for experimental endpoints: immunological, epigenetic and

PK). The Paxgene tube will be stored for subsequent RNA extraction, RNA sequencing and BCR/TCR sequencing.

The schedule for PK/PD sampling is detailed in Appendix 5. Patients will only undergo PK sampling where the site has adequate facilities for processing of samples. Patients attending outpatient clinics will only undergo PK sampling where the site has the facility to accommodate both a baseline sample (screening or day 1 pre-dose) and a post dose sample following dosing on day 1.

For details of sample collection, processing and transfer for all of the above, please refer to Laboratory Manual.

## 5 TREATMENTS

For the purposes of this trial, favipiravir is considered an Investigational Medicinal Product (IMP).

### 5.1 Treatment Arms

Patients who are eligible for this trial will be registered/randomised to receive either:

Control Arm: Standard Treatment for COVID-19 infection

OR

Experimental Arm: Standard Treatment for COVID-19 plus favipiravir:

- Day 1: Loading Dose favipiravir 1800mg (9 x 200mg tablets) 12 hours apart (2 doses)
- Days 2 -10: Maintenance Dose favipiravir 800mg (4 x 200mg tablets) every 12hours (18 doses).

Subjects entering the study with a Child-Pugh liver impairment of grade A should receive the same loading dose but a reduced maintenance dose of favipiravir 600 mg twice daily on Days 2 through 10.

***It is strongly advised that the first dose of favipiravir is administered within 24 hours of the treating clinician receiving a positive valid SARS-CoV-2 test result.***

Treatment to continue until complete, unless there are unacceptable toxicities or other appropriate reasons for stopping treatment before completion.

## 5.2 Specific Drug Information

### 5.2.1 Favipiravir

Favipiravir is considered IMP for the purposes of this trial.

Chemical structure of favipiravir:

[figure not shown]

Favipiravir is supplied as light yellow round film-coated tablets at the dosage strength of 200mg per tablet. They are supplied in 100 tablet packs containing tablets in blister packaging. Refer to favipiravir Investigator Brochure for information regarding the physical and chemical properties and a list of excipients. Favipiravir should be stored at 15° to 30°C and shielded from direct light and moisture.

## 5.3 Dispensing, Accountability and Administration

The investigator or a delegated individual (e.g. pharmacist) must ensure that the trial IMP are dispensed in accordance with the protocol, local Standard Operating Procedures and applicable regulatory requirements.

### 5.3.1 Favipiravir Dispensing and Accountability

Batch number, dose prescribed, quantity and expiry of the drug supplied must be recorded in the accountability logs. Both bulk stock and individual patient accountability logs must be completed. Favipiravir course should be dispensed for inpatient use in a container and with instructions applied that make it suitable for use at the time of discharge, should continuation be required after discharged to complete the course. Full instructions regarding management, labelling and accountability of favipiravir is given in the IMP Management Document for the trial.

### 5.3.2 Favipiravir Administration

Favipiravir should be administered every 12 hours with no consideration of timing required in relation to food. If the patient vomits at any time after administration, dosage should not be replaced. If a dose is missed, it can be taken within 4 hours of the planned time and the next dose should be taken at the original dosing planned dosing time. After this time the missed dose should not be replaced. Favipiravir is not suitable for nasogastric administration.

Favipiravir may cause some people to become more sensitive to light and cause a rash or other mild skin reaction. Patients should be advised to avoid strong sunlight or UV light (e.g. a sun bed) during and for 1 week after favipiravir treatment, and to cover any sun exposed areas of skin and use sunscreen with high sun protection factor (SPF).

***It is strongly advised that the first dose of favipiravir is administered within 24 hours of the treating clinician receiving a positive SARS-CoV-2 test result.***

If a patient on the Experimental Arm of the trial is no longer able to take favipiravir because they are no longer able to swallow tablets (for example, if they are being treated with mechanical ventilation), all trial assessments should continue whenever possible.

## 5.4 Trial Drug Supplies

### 5.4.1 Favipiravir Supplies

Favipiravir will be provided free of charge from FUJIFILM Toyama Chemical Co., Ltd. to sites via Clinigen Group Plc for use by patients in this trial and will be commercial stock from Japan over-labelled as trial specific investigational medicinal product trial stock.

- Favipiravir will be packaged into boxes containing 100 tablets packs containing tablets in blister packaging. The supplies will be in commercial livery as licensed stock from Japan, with the details in Japanese. Clinigen will have applied labels that comply with Good Manufacturing Practice and in accordance with local regulatory labelling requirements (Annex 13 of Eudralex Volume 4). The labels will state that the trial drug is for clinical trial use only
- Only those supplies intended for use in the trial should be dispensed to the trial participants and clinical trial supplies must be dispensed in accordance with the trial protocol

- Upon arrival of investigational product at site, site personnel should check the supplies for damage and verify proper identity, quantity, integrity of seals and report any deviations or product complaints to the CRUK CTU upon discovery
- All trial medications must be stored in a secure area with access limited to the investigator and authorised site staff and under physical conditions that are consistent with the specific requirements of the medication. Favipiravir should be stored at 15° to 30°C and shielded from direct light. For batch specific instructions and information on the shelf life of favipiravir see the packaging.
- Full instructions regarding management, labelling and accountability of favipiravir is given in a separate IMP Management Document for the trial

### **5.5 Trial Treatment Recording**

Reasons for any dose delays, dose reductions and dose omissions of trial drugs should be documented in the appropriate section of the CRF and in the patient's medical records

For patients self-administering favipiravir at home, a diary will be provided to record the time each dose was taken, and the reason for any missed doses – patients will be asked to return the completed diary along with any remaining drug or empty containers at a follow-up clinic visit.

### **5.6 Concomitant Therapy**

All concomitant therapy taken at any point from 4 weeks before registration/randomisation up to and including the end of treatment visit must be documented in the patient's medical records along with dose, frequency and therapeutic indication.

### **5.7 Prohibited Therapy/Prohibited Medications/Permitted Concomitant Medications**

- Other medication taken for treatment of COVID-19 whether investigational or approved may be permitted on a case by case basis – please contact Sponsor & CI to discuss.
- When remdesivir is added to the UK protocols as part of the standard of care for treatment of COVID19, co-prescribing will be permitted with favipiravir with regular monitoring of LFTs according to the combined protocol schedules for both medications. remdesivir prescription must be recorded in the patient CRF.
- Dexamethasone has been shown to have benefit in the treatment of COVID-19 in certain groups of patients and is being adopted into standard care. Treatment with

dexamethasone is permitted concurrently with favipiravir. Coadministration of dexamethasone with favipiravir has not been studied. Dexamethasone is a substrate of CYP3A4 and a moderate inducer of this enzyme. Favipiravir does not appear to be metabolised by this pathway – but there is limited data and Investigators must be vigilant to the possibility of interactions. Dexamethasone prescription must be recorded in the patient CRF.

Details of the administration of any prohibited therapies will be collected on the trial CRFs and must be reported as a protocol deviation as per section 11.3.

#### **5.7.1 Interactions with other medications**

There have been limited direct interaction studies of favipiravir and there is limited clinical experience of wide use of the product. Investigators must be vigilant to the possibility of interactions with other medicines other than those listed below.

- Paracetamol AUC may be increased and dosage should be restricted to 3g in 24h – this may require to be lowered further for lower bodyweight patients. This should be highlighted on the patient's notes, and clear instruction given to patients treated in the community.

The following may interact with favipiravir and risks and benefits should be carefully considered prior to treatment with the following:

- Any other anti-viral medication whether investigational or approved.
- Any drugs known to significantly inhibit Aldehyde Oxidase activity (e.g., pyrazinamide, amitriptyline, chlorpromazine, clomipramine, clozapine, erythromycin, ketoconazole, nortriptyline, quetiapine, raloxifene, perphenazine, promethazine, propafenone, tamoxifen, thioridazine).

Any drugs metabolized by the Aldehyde Oxidase pathway (e.g., famciclovir, hydralazine, lamivudine, sulindac, zaleplon, ziprasidone).

- Any drugs that interact with xanthine oxidase pathway, e.g. theophylline and aminophylline.
- Any drugs metabolised by CYP2C8, e.g. concentration of repaglinide concentration may be increased.

- Drugs with possible drug-drug interactions (concomitant medications requiring particular attention – see the Investigator Brochure).

This list is not exhaustive and IB should be checked in addition.

### **5.7.2 Adverse Reactions**

Adverse reactions have been noted in the US and Japanese clinical studies where lower doses and shorter durations of treatment were used than in this protocol. The most common reactions included increases in blood uric acid levels, nausea, vomiting, diarrhoea, headache, ALT&AST increases, UTI, decreases in neutrophil and white blood cell count and increases in blood triglycerides.

Further details can be found in the Investigator's Brochure.

### **5.8 Dose Modifications for toxicity**

A subject should be removed from favipiravir treatment if one of the following criteria is met:

- AST or ALT > 5 x ULN
- ALT or AST > 3 x ULN AND total bilirubin > 2X ULN
- AST or ALT > 3 x ULN AND patient has right upper quadrant pain or eosinophilia
- Uric acid >20 mg/dL (1.2 mmol/l)
- Any other ≥ Grade 3 adverse event considered by the study team to be due to the trial drug.

Any > 3 x ULN AST or ALT event should be reported as a AE of Special Interest using the SAE form provided by the CRUK CTU Pharmacovigilance department.

No dose reductions are required for reductions in renal function if they occur during treatment. There no data for treatment with favipiravir during haemofiltration or dialysis – if this occurs during treatment the Sponsor & CI should be contacted to discuss the risk-benefit of continuing treatment for the individual case.

If remdesivir is administered in combination with favipiravir, EGFR must be >30ml/min and LFTs must be monitored daily during treatment with remdesivir. The stopping rules above for raised

transaminases apply for the combination treatment. Ensure remdesivir SmPC or equivalent source of information is consulted before initiating the combination treatment with favipiravir.

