#### **Exclusion criteria**

1. Renal impairment requiring, or likely to require, dialysis or haemofiltration
2. Pregnant or breastfeeding
3. Of child bearing potential\* (women), or with female partners of child bearing potential (men) who do not agree to use adequate contraceptive measures for the duration of the study and for 3 months after the completion of study treatment
4. History of hereditary xanthinuria
5. Other patients judged unsuitable by the Principal Investigator or sub-Investigator
6. Known hypersensitivity to favipiravir, its metabolites or any excipients
7. Severe co-morbidities including: patients with severe hepatic impairment, defined as:
  - (greater than Child-Pugh grade A- see Appendix 4,
  - AST or ALT  $> 5 \times \text{ULN}$
  - AST or ALT  $> 3 \times \text{ULN}$  and Total Bilirubin  $> 2 \times \text{ULN}$
8. More than 96 hours since first positive COVID19 test sample was taken

9. Unable to discontinue contra-indicated concomitant medications (section 6.7)

\* Non-childbearing potential must be evidenced by fulfilling one of the following criteria at screening:

- Post-menopausal defined as aged more than 50 years and amenorrhoeic for at least 12 months following cessation of all exogenous hormonal treatments.
- Prior irreversible surgical sterilisation by hysterectomy, bilateral oophorectomy or bilateral salpingectomy but not tubal ligation

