#### **Exclusion criteria**

1. Renal impairment requiring dialysis or haemofiltration
2. Pregnant or breastfeeding
3. Of child bearing potential\* (women), or with female partners of child bearing potential (men) who do not agree to use adequate contraceptive measures for the duration of the study and for 3 months after the completion of study treatment
4. History of hereditary xanthinuria

5. Xanthine urinary calculi
6. Other patients judged unsuitable by the Principal Investigator or sub-Investigator
7. Known hypersensitivity to favipiravir, its metabolites or any excipients
8. Severe co-morbidities including patients with severe hepatic impairment defined as:
  - greater than Child-Pugh grade A (Appendix 4)
  - AST or ALT > 5 x ULN
  - AST or ALT > 3x ULN and Total Bilirubin >2xULN
9. More than 96 hours since first positive COVID19 test was taken.
10. Unable to discontinue contra-indicated concomitant medications (section 6.7)

\* Non-childbearing potential must be evidenced by fulfilling one of the following criteria at screening:

- Post-menopausal defined as aged more than 50 years and amenorrhoeic for at least 12 months following cessation of all exogenous hormonal treatments.
- Irreversible surgical sterilisation by hysterectomy, bilateral oophorectomy or bilateral salpingectomy but not tubal ligation

**There will be no exception to the eligibility requirements at the time of registration/randomisation. Queries in relation to the eligibility criteria should be addressed via contact with the CTU prior to registration/randomisation. Patients are eligible for the trial if all the inclusion criteria are met and none of the exclusion criteria apply.**

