### 3.5 Withdrawal

#### 3.5.1 Withdrawal of Patients from Trial Treatment

Patients have the right to withdraw from trial treatment at any point for any reason. Similarly, the investigator may withdraw patients from the trial drug in the event of intra-current illness, AEs, SAEs, SUSARs, protocol violations or any other relevant reasons. **If a patient withdraws from treatment early, they should be followed up as per trial schedule.**

A subject must be discontinued from the trial for any of the following reasons:

- The subject or legal representative withdraws consent
- Patient meets stopping rules criteria (see Section 6.8)
- Investigator's decision to withdraw the subject
- The subject has a confirmed positive serum pregnancy test
- Noncompliance with trial treatment or procedure requirements
- Administrative reasons

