#### **5.8.1 Treatment Interruptions**

No planned treatment interruptions are permitted.

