#### **5.8.2 Dose Modifications during Favipiravir Treatment**

No dose modifications once on treatment are permitted for toxicity. Please see instructions for stopping in section 6.8.

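### One of the three transaminase rules for stopping favipiravir has no matching exclusion, so a patient can meet it already at randomisation

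*Protocol*

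**What the plan says.** Section 5.8 (Dose Modifications for toxicity) lists criteria, any one of which is enough to take a patient off favipiravir. Three concern transaminases: AST or ALT above 5 times ULN; above 3 times ULN with total bilirubin above 2 times ULN; and "AST or ALT > 3 x ULN AND patient has right upper quadrant pain or eosinophilia". None refers to the baseline value or exempts an abnormality present before dosing.

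The hepatic exclusion stands in section 3.2 (item 8) and in the Trial Summary (item 7, introduced by "Severe co-morbidities including: patients with severe hepatic impairment, defined as"). Both versions have the same three limbs: Child-Pugh worse than grade A, transaminases above 5 times ULN, and "AST or ALT > 3x ULN and Total Bilirubin >2xULN". Neither mentions right upper quadrant pain or eosinophils.

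Section 3.2 defines eligibility strictly: "Patients are eligible for the trial if all the inclusion criteria are met and none of the exclusion criteria apply". Both lists also have a judgement criterion: "Other patients judged unsuitable by the Principal Investigator or sub-Investigator".

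On the action to take, section 5.8.1 states "No planned treatment interruptions are permitted" and section 5.8.2 states "No dose modifications once on treatment are permitted for toxicity". Section 3.5.1 gives, among the reasons for which discontinuation is mandatory, "Patient meets stopping rules criteria (see Section 6.8"). The protocol has no section 6.8; the rules are in 5.8.

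**The concern.** For two of the three transaminase rules the entry limit equals the stopping limit, so nobody can enter already meeting the rule. For the third there is no entry limit, and an otherwise eligible patient can satisfy it on the day of randomisation.

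Neither way of reading section 5.8 handles that patient well. If the rule applies from the outset, a patient allocated to favipiravir must be stopped immediately, because interruption and dose modification are ruled out, and then counts in that arm untreated. If the rule applies only to findings that arise on treatment, the patient starts the drug with a hepatic signal that the protocol itself regards as grounds for stopping. Section 5.7.2 lists ALT and AST increases among the commonest reactions, seen at lower doses and shorter courses than those used here.

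The gap matters more for outpatients. Their schedule has routine bloods at screening and next at day 15, after the ten-day course has ended, with telephone assessments on days 1 to 10. Screening is therefore their only scheduled laboratory check before or during dosing.

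**Working it through.** The check is a line-by-line comparison; the plan states no figure to reproduce.

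**Step 1: removal rules against exclusions.**

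| Transaminase rule in section 5.8 | Section 3.2, item 8 | Trial Summary, item 7 |
|---|---|---|
| > 5 x ULN | present, same threshold | present, same threshold |
| > 3 x ULN with bilirubin > 2 x ULN | present, same thresholds | present, same thresholds |
| > 3 x ULN with right upper quadrant pain or eosinophilia | absent | absent |

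Rules without a matching exclusion: 3 - 2 = 1 of 3.

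**Step 2: does the Child-Pugh limb close the gap?** Appendix 4 scores encephalopathy, ascites, bilirubin, albumin and prothrombin time or INR. Transaminases, abdominal pain and eosinophils do not enter the score. It does not.

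**Step 3: a test case.** Take ALT at 4 x ULN, bilirubin not above 2 x ULN, Child-Pugh no worse than A, and right upper quadrant pain.

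- The > 5 x ULN exclusion does not apply, since 4 < 5.
- The combined exclusion does not apply, since its bilirubin condition fails.
- The Child-Pugh exclusion does not apply.
- The third removal rule in 5.8 is met, since 4 > 3 and the sign is present.

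The patient passes every objective hepatic criterion and already qualifies for removal.

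**Step 4: could it be seen at screening?** Yes. Table 2 includes AST, ALT and a white-cell differential, and sections 4.2.1 and 4.2.2 both schedule these bloods and a clinical examination before the first dose.

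**Step 5: size.** The protocol gives no frequency for transaminases at 3 to 5 x ULN, for right upper quadrant pain or for eosinophilia at entry, so the number affected cannot be derived. Two calculations bound it, using the planned 151 patients per arm.

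- Frequency needed for one expected favipiravir patient: 1 / 151 = 0.0066, or 0.66% of entrants. This needs no assumption.
- Illustration with assumed inputs: 2% to 5% of entrants at 3 to 5 x ULN, of whom 1% to 10% have either sign.
  - Low end: 0.02 x 0.01 = 0.0002 of entrants; 151 x 0.0002 = 0.03 patients.
  - High end: 0.05 x 0.10 = 0.005 of entrants; 151 x 0.005 = 0.76 patients.

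Both ends fall below one expected patient, because 0.5% is below 0.66%.

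**The case against.** The strongest reply is that section 5.8 is a toxicity rule. Its title, its reference to removal from treatment and its final criterion, which concerns other events attributed to the drug, all suggest findings that arise on treatment. On that reading a pre-existing abnormality triggers nothing, and no baseline exception is needed. This is the more natural reading and it weakens the picture of a patient randomised and stopped at once. It does not dispose of the point, because the patient is then dosed with a sign combination that the protocol calls a reason to stop.

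Second, stopping limits need not equal entry limits, and the protocol states no such principle. The uric acid rule in 5.8 also lacks an exclusion, so two of its four laboratory-based rules are unmatched. That is fair: the omission may not be an oversight. Nothing is claimed here about uric acid. Within the transaminase rules, however, the pattern is exact for two and broken for the third.

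Third, an investigator who sees raised transaminases with pain can use the judgement criterion, and the hepatic item is worded openly enough to allow it. This is a real safeguard, but it permits exclusion without requiring it and names no threshold.

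Fourth, inpatients have routine bloods on days 1, 3 and 8, so a persisting abnormality would be seen. That stands for inpatients. It does not help outpatients, nor inpatients discharged early, who move to the outpatient schedule.

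Finally, section 3.5.1 speaks of discontinuation from the trial and section 5.8 of removal from the drug. These are different actions, so 3.5.1 should not be used to harden 5.8. The case does not depend on it, and its reference to section 6.8 is a separate clerical slip.

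**Conclusion.** The concern holds, as a minor point of patient safety and internal consistency. One of three transaminase removal rules has no counterpart in either exclusion list, and only investigator discretion stands between such a patient and randomisation. That follows from the text and needs no assumption.

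The practical size is small. Under the assumed frequencies fewer than one favipiravir patient is expected to be affected (0.03 to 0.76), and those frequencies are not from the documents. Sample size and error rates are untouched, and no effect on the primary analysis is claimed.

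**What to change.** Add one limb to the hepatic exclusion in section 3.2 (item 8) and in the Trial Summary (item 7): AST or ALT above 3 times ULN together with right upper quadrant pain or eosinophilia. All three transaminase removal rules then have a matching entry limit.

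The cost is one line in two places. The bloods, the differential and the clinical examination are already done at screening for inpatients and outpatients, so no procedure is added. A very small number of patients become ineligible. No change is needed to the visit schedule or to the safety analysis in section 7.1.5.
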